**Methods and analysis::**

This large, prospective, multicenter cohort study started in May 2015 in Shenyang. Six hundred children diagnosed with HSPN were recruited from 3 institutions and are followed-up every 2 to 4 weeks till May 2020. Detailed information of participants includes general information, history of treatment, physical examination, and symptoms of TCM is taken face-to-face at baseline.

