### Study design

2.1

This large, prospective, multicenter cohort study is being conducted in 3 institutions between May 2015 and May 2020. Six hundred participants are recruited and divided into 2 cohorts, with 300 individuals per cohort. All cohorts will undergo a 12-week treatment and a 12-month follow-up period. Participants will be asked to visit the clinicians every 2 weeks during the treatment period and once a month during the follow-up period. The feasibility and preciseness of the whole process are supervised by 1 to 2 supervisors.

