### Study settings and participants

2.2

HSPN patients are being recruited from outpatient and inpatient departments of three large comprehensive hospitals in China, including the Affiliated Hospital of Liaoning University of TCM, the First Affiliated Hospital of China Medical University, and the Shengjing Hospital of China Medical University. The patient screening will be conducted by clinicians who are not involved in the study. If a patient meets the study criteria, the clinician who is responsible for the patient screening will provide him/her with written information, explain the study in detail in an understandable language and obtain the written consent if he/she is willing to take part in the study. Informed consent must be obtained for all patients enrolled in the study. The eligible children with HSPN taking CHM in one of the above 3 hospitals were classified as cohort 1 and participants received WM without CHM belong to cohort 2. Trials that combine CHM with WM will be included, if the cohort 2 received the same WM as the cohort 1. Doctors of traditional Chinese medicine in the above hospitals prescribe CHM for patients according to their symptoms and signs, tongue manifestations, and pulse condition. The study flow chart is shown in Figure 1.

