### Statistical analysis

2.9

The statistical analysis will be conducted by a statistician of the Institute of Basic Research in Clinical Medicine, China Academy of Chinese Medical Sciences, Beijing, China. The statistician is blinded to the entire trial and will use SAS 9.1.3 (SAS Institute, Cary, NC, USA) and SPSS Version 13.0 (SPSS Inc., Chicago, IL) software. To test the hypotheses about associations between baseline risk factors and HSPN incidence, hazards ratios will be computed using the Cox proportional hazard regression models. Baseline differences between the groups will be assessed with the use of Student's *t*-test for normally distributed continuous variables and the nonparametric Mann–Whitney *U*-test for non-normally distributed variables. Comparisons between the groups will be conducted using an analysis of covariance (ANCOVA) with the baseline as the covariate. For efficacy analysis, changes from the baseline to the endpoint of treatment in scores will be tested with repeated measured analysis of variance (ANOVA). Within each group, differences will be assessed with paired t-test for normally distributed data and the Wilcoxon signed-rank test for non-normally distributed data. Safety will be assessed by participant compliance and adverse events. For analysis of the final dataset, missing data will be filled in using the last observation carried forward (LOCF) approach. A *P* value <.05 is considered significant.

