## Discussion

3

HSPN is a major public health problem and accounts for 78.9% of secondary glomerulopathy in children.^[22]^ Currently, TCM plays a considerable role in symptom and quality of life improvement for HSPN children patients in China and worldwide. In this study, we propose the use of CHM to improve the clinical management of HSPN. A prospective cohort design is employed in the study, and 600 HSPN children patients will be treated as subjects.

To guarantee the quality of the study programs, only patients who meet the inclusion criteria will be recruited. In addition, patients will be excluded if they also suffer from nephritic syndrome, rapidly progressive glomerulonephritis, chronic glomerulonephritis, respiratory diseases, digestive diseases, and liver or mental diseases. The medical therapies associated with these afflictions may interact with the planned interventions, resulting in difficulty in interpreting the clinical results.

It is worth mentioning that we adopted an online clinical research data-capture computer system to collect the data. To minimize the bias and artificial errors of human data management, each patient record will be typed by three researchers and verified before storing. Once stored, the data will be visible to the statisticians and supervisors of this study. They will not be able to modify the data entries. The clinical appraisers and statisticians will be kept unaware of whether a participant belongs to the experimental or the control group. We attempt to establish the chronic disease management programs incorporating information technology (IT) solutions for children with HSPN and explore the effective model for long-term treatment through disease control, psychological intervention, and social support.

The outcomes in the follow-up will include renal events, mortality rate, and adverse events. These outcomes will be easy to assess with only a few questions. The physicians who follow the entire process of the study are familiar with patients and are experienced interviewers. These measures will guarantee the quality of the follow-up. In conclusion, this prospective cohort study will identify whether CHM is helpful for the treatment of HSPN in pediatric patients. The results of this research may generate scientific evidence for further confirmatory studies.

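### Cohorts are formed by treatment received, but the only covariate named is the baseline and no adjusted analysis is named for remission or recurrence, so the CHM comparison is open to confounding

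*Protocol article*

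**What the plan says.** **Design.** Section 2.1 describes a prospective multicentre cohort study: "Six hundred participants are recruited and divided into 2 cohorts, with 300 individuals per cohort". Section 2.2 defines the cohorts by treatment: "The eligible children with HSPN taking CHM in one of the above 3 hospitals were classified as cohort 1". The comparator is likewise set by what the child was given: "participants received WM without CHM belong to cohort 2". No randomisation, matching or stratification is described. Section 2.2 also says that TCM doctors in these hospitals "prescribe CHM for patients according to their symptoms and signs, tongue manifestations, and pulse condition". Where CHM is combined with WM, cohort 2 is to receive the same WM.

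**Outcomes.** Section 2.5.1 names two primary outcomes, remission rate and recurrence rate.

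**Analysis (section 2.9).** The between-group method is "Comparisons between the groups will be conducted using an analysis of covariance (ANCOVA) with the baseline as the covariate". Changes in scores are tested by repeated-measures ANOVA. Baseline differences are examined by t-test or Mann–Whitney test, and no later step depends on the result. A Cox model is named, but for baseline risk factors and HSPN incidence.

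**Baseline data (Abstract).** "Detailed information of participants includes general information, history of treatment, physical examination, and symptoms of TCM is taken face-to-face at baseline".

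**Intended conclusion (Discussion).** "this prospective cohort study will identify whether CHM is helpful for the treatment of HSPN in pediatric patients".

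**The concern.** When treatment is not randomised, the cohorts can differ at entry in ways that also predict remission and recurrence, such as age, clinical class, earlier treatment or the hospital attended. A crude difference between cohorts then mixes any CHM effect with these differences. Here the one covariate that the plan names is the baseline, most naturally read as the baseline value of the outcome. That can help for a symptom score. It does not carry over to remission and recurrence: every enrolled child has HSPN at entry, so there is no baseline value of these outcomes to adjust for. If section 2.9 is followed as written, the primary comparison has no stated protection against confounding, although its result is to be read as an answer on whether CHM helps.

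**Working it through.** **1. What each named method covers**

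| Method in section 2.9 | Applied to | Adjusts the CHM effect on remission or recurrence? |
|---|---|---|
| t-test, Mann–Whitney | baseline differences, continuous variables | No; these describe or test imbalance only |
| ANCOVA, baseline as covariate | between-group comparisons | No; it suits a continuous outcome, and the rates have no baseline value |
| Repeated-measures ANOVA | change in scores | No; scores only, no covariate stated |
| Paired t-test, Wilcoxon | change within each group | No; not a between-group comparison |
| Cox model | baseline risk factors and HSPN incidence | No; not assigned to the CHM effect, and all enrolled children already have HSPN |

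No row adjusts the primary comparison for a patient characteristic or for centre.

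**2. The plan's own yardstick**

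Section 2.6 assumes response rates of 53% and 40%, a difference of 13 points, with 250 per group for 90% power at two-sided 5%. The 250 does not reproduce. The pooled two-sided formula gives 308 per group, and 250 per group gives 83% power. A one-sided 5% test gives 251. That is a separate matter. What is needed here is the 13 points.

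**3. Hypothetical illustration of a confounder left out**

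None of the following inputs is in the document. Assume that CHM has no effect and that a severe class has 30% remission against 60% in milder classes. Assume that the severe class makes up 40% of the CHM cohort and 60% of the WM cohort.

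- CHM: 0.40 × 0.30 + 0.60 × 0.60 = 0.48
- WM: 0.60 × 0.30 + 0.40 × 0.60 = 0.42
- Spurious difference: 0.48 − 0.42 = 0.06, and 6/13 = 46% of the planned effect

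Take a crude two-sided 5% test of two proportions, 300 per cohort:

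- SE under the null, pooled rate 0.45: √(2 × 0.45 × 0.55 / 300) = 0.0406
- SE of the difference: √((0.48 × 0.52 + 0.42 × 0.58) / 300) = 0.0405
- Rejection probability: Φ((0.06 − 1.96 × 0.0406) / 0.0405) ≈ Φ(−0.48) ≈ 0.31, against the nominal 0.05

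With 250 per cohort it is about 0.27.

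**4. Range under other assumptions**

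Again with no CHM effect, fix cohort 2 at 40% response and take 250 per cohort, with one binary prognostic factor left out:

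| Odds ratio of the factor | Prevalence, cohort 1 / cohort 2 | Spurious difference | False-positive rate |
|---|---|---|---|
| 2 | 60% / 40% | 3.3 points | 12% |
| 2 | 70% / 30% | 6.7 points | 33% |
| 3 | 70% / 30% | 10.6 points | 67% |
| 3 | 80% / 20% | 16.0 points | 95% |

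The direction is assumed too. If the severe share in step 3 is reversed (60% of CHM, 40% of WM), the bias is −6 points and would mask a benefit.

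**The case against.** **The unseen analysis plan may adjust.** Detail may properly be left to it. Here, however, the protocol does state the between-group method and its covariate, and nothing in it points to more. The point is about a stated method that does not suit the design.

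**The design already limits confounding.** Renal insufficiency and the nephritic syndrome, rapidly progressive and chronic classes are excluded, which narrows the severity range. The same-WM rule limits differences in co-treatment. Both help, but four clinical classes and ages 5 to 18 remain, and neither measure balances patients or centres.

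**Baseline adjustment may absorb part of the severity imbalance.** That stands for scores. It does not help the two rates.

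**The claim is softened.** The Discussion adds that the results may feed further confirmatory work. That is fair, but the preceding sentence still promises to settle whether CHM helps.

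**Three stronger readings that the document does not support.**

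- A reader might infer from the hospital names (one TCM hospital, two of a medical university) that hospital determines treatment. Section 2.2 allows CHM at any of the three and gives no cohort-by-hospital split. Centre confounding is possible, not shown.
- A reader might take the sentence on symptoms, tongue and pulse as proof that the child's presentation decides who gets CHM. It can equally describe how a CHM prescription is tailored once chosen. How the choice between CHM and WM alone is made is not stated.
- A reader might take the 31% as the error rate of the planned analysis. It belongs to a crude test of two proportions, which section 2.9 does not name, under invented inputs.

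**Conclusion.** The point holds as follows. Cohorts are defined by treatment received, the stated between-group adjustment is for the baseline only, and no adjusted analysis of the CHM effect is named for remission or recurrence. The comparison is therefore open to confounding, and followed as written it cannot by itself carry the conclusion in the Discussion. To say that it is confounded would go further than the document allows, because neither the imbalance between cohorts nor its direction is known.

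The size cannot be derived from the document. Under the stated assumptions, one omitted factor gives a spurious difference of about 3 to 16 points. The worked case gives 6 points and about 31% false positives at 300 per cohort. These figures show only that plausible imbalances are of the same order as the 13 points that the study is designed to detect.

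**What to change.** In section 2.9:

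1. Make the primary comparison of remission and of recurrence a pre-specified multivariable or propensity-score analysis.
2. Fix the covariates in advance: age, sex, clinical class, baseline urine protein and erythrocytes, history of treatment, and centre. Age and class are needed for eligibility, treatment history is taken at baseline, urine findings belong to the symptom assessment, and case report forms are completed by centre. Sex is presumably part of the general information.
3. Judge balance by standardised differences rather than P values.
4. Tabulate cohort by hospital and check overlap before weighting on hospital. If overlap is poor, compare within those hospitals that contribute both cohorts.
5. Word the conclusion in the Discussion as an adjusted association.

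**Cost.** This is mainly a change of wording and analysis, but power falls. As an approximation, let R² be the share of treatment choice explained by the covariates, so that the effective size is n × (1 − R²). For 53% against 40%, 250 evaluable per cohort and two-sided 5%, power falls from 83% to 79%, 74% and 69% at R² of 0.1, 0.2 and 0.3. For 90% power the need rises from 308 to 308/(1 − R²), about 343, 385 and 440 evaluable per cohort. The R² values are assumptions. If cohort and hospital overlap little, the loss is larger, and within-hospital comparisons may rest on few children. Adjustment also cannot remove confounding by factors that are not recorded.

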#### Secondary outcomes

2.5.2

1.Symptom improvement (such as urine erythrocyte, urine protein, etc)2.Adverse events.

Each symptom or sign will be given a score, and the sum of all scores will be recorded in Table 1.

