### Safety assessment

2.7

For the sake of participant safety, the following biological indicators will be monitored and watched throughout the trial: blood routine, liver function (AST, ALT), renal function (BUN, Cr), and electrocardiography (ECG). Any unexpected symptoms and signs or feelings of discomfort in patients will be recorded as adverse events. For each adverse event, the starting date, ending date, degree, relationship to the trial and potential to trigger patient drop-out from the study will be carefully recorded and considered. If an adverse event occurs, the patient will be monitored until his/her adverse event disappears.

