In this trial, we intend to assess the efficacy and advantage of the use of CHM for the treatment of children with HSPN. We hypothesize that CHM will be an effective and safe way to treat HSPN patients and to reduce the recurrence rate.

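### The safety sentence in section 2.9 counts compliance as safety evidence and leaves out the blood, liver, renal and ECG tests that section 2.7 collects for safety

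*Protocol article*

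**What the plan says.** Four places in the protocol article bear on safety.

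- **Section 2.7, Safety assessment**, lists the tests monitored throughout the study: "blood routine, liver function (AST, ALT), renal function (BUN, Cr), and electrocardiography (ECG". A separate sentence describes adverse events: "Any unexpected symptoms and signs or feelings of discomfort in patients will be recorded as adverse events". Dates, degree and relationship to the trial are then recorded for each event.
- **Section 2.5.2, Secondary outcomes**, has a single safety item, "Adverse events". No laboratory or ECG variable is listed there as a safety outcome.
- **Section 2.9, Statistical analysis**, gives the basis for the safety assessment: "Safety will be assessed by participant compliance and adverse events".
- **The closing paragraph of the Discussion** states the hypothesis: "We hypothesize that CHM will be an effective and safe way to treat HSPN patients and to reduce the recurrence rate".

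**The concern.** The article makes a positive statement about what safety will be judged on, and that statement does not match the safety data it collects.

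First, compliance is not a measure of harm. A treatment that is easy to take but injures the liver or kidney without symptoms would show good compliance. Counting compliance as safety evidence would then favour it.

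Second, liver and renal tests are done largely to find injury before it is felt. If these results reach the safety conclusion only when a child also has a recordable symptom, sign or discomfort, much of the reason for collecting them is lost. The participants are children with kidney disease, so creatinine bears directly on safety.

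At stake is the safety half of the hypothesis. Followed as written, the safety conclusion would rest partly on compliance and could miss a difference between cohorts in symptom-free test abnormalities.

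**Working it through.** There is no figure to reproduce. The check sets the passages side by side.

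1. **Collected for safety (section 2.7):** four groups of tests, namely blood routine, liver function (AST, ALT), renal function (BUN, Cr) and ECG.
2. **Named as the basis for assessing safety (section 2.9):** two items, compliance and adverse events. Compliance measures exposure, so one of the two measures harm. None of the four test groups is named.
3. **Is there a link through the definition of an adverse event?** Section 2.7 covers unexpected symptoms, signs and discomfort. It gives no threshold and no rule that makes an abnormal laboratory or ECG result an adverse event. The tests and the definition stand in separate sentences with nothing joining them.
4. **Is there a link through the outcome list?** Section 2.5.2 names adverse events only, which leads back to step 3.
5. **Is there a link through another sentence in 2.9?** One general sentence reads: "Comparisons between the groups will be conducted using an analysis of covariance (ANCOVA) with the baseline as the covariate". It names no outcome, so it could cover continuous laboratory values. It would not suit a categorical ECG reading. It also compares means, which is a weak way to detect a few children with marked elevations.
6. **Is any test result excluded?** No. The safety sentence does not say that it is exhaustive, and no other passage rules the tests out.

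Taken together, an abnormal test result with a symptom enters the safety result as an adverse event. An abnormal result without one may or may not enter, depending on how the reader takes the word for signs in section 2.7 and the general ANCOVA sentence in section 2.9. With three hospitals completing case report forms, the same ALT rise could be recorded differently from one to another.

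**The case against.** A reader might infer that the laboratory and ECG results never enter the comparison between cohorts, or that only symptomatic events are counted. The documents do not support either reading, for these reasons.

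- **Nothing excludes the tests.** Sections 2.7 and 2.9 can be read as complementary. This stands.
- **The definition of adverse events includes signs.** The article also uses symptom language loosely: section 2.5.2 gives urine red cells and urine protein as examples of symptom improvement. By that usage an unexpected ALT rise might count. This stands as a possible reading, but it leaves the definition ambiguous and does not settle it.
- **The ANCOVA sentence is not confined to efficacy.** The sentence that opens with efficacy comes after it. This stands in part. The ANCOVA sentence is general, whereas the safety sentence is specific and names its two measures.
- **Renal harm has another mention.** The Discussion lists renal events among the follow-up outcomes. The term is not defined, so it is unclear whether a creatinine rise would qualify, and it does nothing for liver, blood or ECG findings.
- **The article is condensed.** Thresholds and safety tables usually sit in a full protocol or analysis plan, and their absence here is no fault. This stands, and the point does not rest on it. It rests on what section 2.9 does say: compliance is named as safety evidence and the monitored tests are not.

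No estimate of the power to detect a laboratory signal is offered. The documents give no rate of test abnormality, so any such figure would be an unanchored assumption.

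**Conclusion.** The point holds as a mismatch between two sections, together with one wrongly chosen measure. Section 2.9 treats compliance as evidence of safety, which it is not, and omits all four groups of tests that section 2.7 collects for safety. The route for a symptom-free abnormality into the safety result is unclear, but it is not shown to be closed.

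The size cannot be put as a bias or a loss of power. It is a risk that the safety conclusion rests on an exposure measure and misses silent liver or renal changes. The conclusion assumes that the article's safety sentence reflects the plan. A fuller document could already specify laboratory tables. Even then the compliance wording and the mismatch in the published text would need correcting. The change is worth making because the data are already being collected and the hypothesis makes a safety claim.

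**What to change.** Reconcile sections 2.7 and 2.9 with three changes.

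1. **Section 2.9:** replace the safety sentence with wording such as: *Safety will be compared between cohorts by the proportion of children with any adverse event and the proportion with any new clinically significant abnormality in blood routine, AST/ALT, BUN/Cr or ECG, with differences and 95% confidence intervals.*
2. **Section 2.7:** state whether a clinically significant abnormal test result is recorded as an adverse event, so that all three hospitals record it alike.
3. **Compliance:** report it as a description of treatment exposure, not as safety.

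The cost is a few sentences, one more table and a few more comparisons. No new data are needed, and no treatment or visit changes.

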#### Primary outcomes

2.5.1

The primary outcomes of this study are remission rate and recurrence rate of HSPN.

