### Sample size calculation

2.6

According to the response rates of treatment, the cohort 1 and the cohort 2 were 53% and 40%, respectively. It was estimated that 250 patients of each group would be sufficient to achieve 90% power in detecting treatment differences, based on a 2-sided alpha at a significance level of 0.05. Meanwhile, considering a dropout rate of 20%, we concluded that a total of 300 patients for each cohort would need to be recruited to ensure significant results.

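### LOCF as the only missing-data method biases both primary rates downward, and biases the cohort comparison if dropout differs between the cohorts

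*Protocol article*

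**What the plan says.** Section 2.9 (Statistical analysis) of the protocol article states that, when the final dataset is analysed, "missing data will be filled in using the last observation carried forward (LOCF) approach". The rule covers the final dataset as a whole. No other approach to missing data and no sensitivity analysis is named there.

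Section 2.5.1 sets the endpoints: "The primary outcomes of this study are remission rate and recurrence rate of HSPN". Section 2.1 sets the time frame: "All cohorts will undergo a 12-week treatment and a 12-month follow-up period". Section 2.6 allows for 20% dropout, as one figure for both cohorts with no split by period. Section 2.8 schedules seven visits in the treatment period (baseline and every second week to week 12) and monthly visits afterwards, with a phone call when a follow-up visit is missed. Exclusion criterion 6 in section 2.4.3 removes patients whose incomplete data affect the judgement of efficacy and safety.

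**The concern.** Remission and recurrence are both changes of state over time. LOCF assumes that a child's state freezes at the last visit. The Introduction itself describes symptoms as prone to return after long treatment, so that assumption is hard to defend over a year of follow-up.

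The two primary rates are affected in different ways:

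- **Recurrence.** A child lost in month 3 while in remission is scored as recurrence-free at month 12.
- **Remission.** A child lost at week 4 before remitting is scored as never remitting.

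Both errors lower the reported rate. If one cohort loses more children than the other, part of the dropout difference appears as a treatment difference. The cohorts are defined by the treatment received (section 2.2), so nothing in the design ensures equal loss. The hypothesis at the end of the article includes a lower recurrence rate, and recurrence has the longest period at risk.

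**Working it through.** **Inputs from the article.** 300 children per cohort, 20% dropout, response rates of 53% and 40% (section 2.6); 12 weeks plus 12 months, about 12 + 52 = 64 weeks (section 2.1); visits at weeks 0, 2, 4, 6, 8, 10 and 12 (section 2.8).

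**The plan's own figures.** 20% of 300 is 60 children per cohort whose final status could be a carried-forward one. The 300 equals 250 × 1.2. The stated 250 per group does not reproduce for 53% versus 40% at 90% power and two-sided 0.05 (308 by the usual formula). That is a separate matter, and nothing below depends on it. The plan gives no figure for the effect of LOCF.

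**Assumptions, not in the article.** A true 12-month recurrence risk of 30% (20% and 40% also shown); remission of 46.5%, the midpoint of 53% and 40%, accruing linearly to week 12 and holding once reached; loss of 10%, 20% or 30%, unrelated to outcome. Section 2.6 does not tie its response rates to week-12 remission, so 46.5% is only a convenient value.

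**Recurrence.** With constant rates of recurrence λ and loss μ over one year, LOCF reports

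λ/(λ+μ) × [1 − exp(−(λ+μ))].

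For a true 30%, λ = −ln 0.70 = 0.3567.

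| Loss in follow-up | μ | Recurrence under LOCF |
|---|---|---|
| 10% | 0.1054 | 28.6% |
| 20% | 0.2231 | 27.1% |
| 30% | 0.3567 | 25.5% |

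Loss of 10% versus 30% with no true difference gives a false gap of about 3 points, in favour of the cohort that loses more. With a true 20% or 40%, 20% loss reads as 18.0% or 36.2%, and the 10%/30% gap is 2.1 or 4.0 points.

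These figures put the whole loss into the 12 months of follow-up. If it is spread evenly over 64 weeks, 20% × 12/64 = 3.75% goes in treatment and 16.25% in follow-up, which is 16.25/96.25 = 16.9% of those entering follow-up. The 30% then reads as 27.5%. Loss of 10% versus 30% becomes 8.3% versus 25.8% in follow-up and reads as 28.8% versus 26.2%. The gap is still about 2.7 points.

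**Remission.** If lost children leave in equal shares after the visits at weeks 0 to 10, their average carried-forward remission is 46.5% × (5/12) = 19.4%. With d the share lost during treatment, LOCF reports

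46.5% − d × 46.5% × (7/12) = 46.5% − d × 27.1%.

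| Total loss | All loss in weeks 0–10 | Even loss over 64 weeks (d × 12/64) |
|---|---|---|
| 10% | 43.8% | 46.0% |
| 20% | 41.1% | 45.5% |
| 30% | 38.4% | 45.0% |

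Loss of 10% versus 30% gives a false gap of 5.4 points in the first case and 0.2 × (12/64) × 27.1 = 1.0 point in the second.

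**A true difference with equal loss.** LOCF multiplies both rates by 1 − d × 7/12. The planned 13 points become 13 × 0.883 = 11.5 points if all 20% is lost in weeks 0 to 10, and 13 × 0.978 = 12.7 points if loss is even over 64 weeks.

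**The case against.** - **The LOCF sentence may be meant for scores.** It follows ANCOVA, repeated-measures ANOVA and paired tests, and the article names no test for the primary rates. But its wording covers the final dataset without restriction, so as written it reaches the rates.
- **Missingness is reduced by design.** Section 2.8 provides phone contact, and the Discussion says that follow-up outcomes need only a few questions. This may lower the loss. A call cannot measure urine erythrocytes or protein, and cannot reach a child who is truly lost.
- **Lost children may be excluded rather than filled in.** Exclusion criterion 6 and a sample size built on 250 of 300 point that way, so it is not established that every dropout would enter the rates by LOCF. Excluding children for incomplete data is itself selective, and the article does not say how this fits with filling in missing values.
- **With equal dropout the test is sound under the null.** True: with equal loss and equal true rates the type I error stays at 5%. The reported rates are still too low, and a true difference shrinks.
- **A separate analysis plan may add sensitivity analyses.** It may, but the article itself fixes LOCF as the method.

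A reader might also infer that LOCF makes the standard errors of the primary rates too small. The documents do not support that. A binary status carried forward depends only on that child's own observed data, so the binomial standard error is right for the quantity that LOCF estimates. The fault is bias in that quantity.

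**Conclusion.** The point holds and should be corrected. LOCF is unsuitable as the sole method for these primary outcomes, most clearly for recurrence. Under the assumptions shown, 20% loss lowers a 30% recurrence risk by about 3 points, and loss of 10% versus 30% creates a false gap of about 3 points. For remission the false gap runs from about 1 point (loss even over 64 weeks) to 5.4 points (all loss in weeks 0 to 10).

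The downward direction for remission assumes that remission, once reached, lasts to week 12. A child lost in remission who relapsed before then would count the other way.

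Two stronger readings are not supported:

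- **5.4 points as the expected distortion.** That is about 40% of the planned 13 points (5.4/13), but it is the upper end of the illustration. Section 2.6 gives no time split for the 20%.
- **Dropout will differ, and will favour one treatment.** Section 2.6 gives one rate for both cohorts. The non-randomised design makes a difference possible, no more. Higher loss would also make a cohort look better on recurrence and worse on remission, so no consistent advantage follows.

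**What to change.** Replace LOCF as the main method in section 2.9:

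- **Recurrence:** time to first recurrence among children who reached remission, censored at the last assessment that can establish recurrence status (Kaplan–Meier and Cox). The Cox model now in section 2.9 is assigned to baseline risk factors and HSPN incidence, not to this comparison.
- **Week-12 remission:** multiple imputation using cohort, baseline covariates and earlier visits, with missing counted as no remission as a sensitivity analysis.
- **Symptom scores:** a mixed model for repeated measures on the observed visits.
- **LOCF:** at most a sensitivity analysis.

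State how exclusion criterion 6 on incomplete data fits with the handling of missing data, and report loss by cohort and by period.

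The cost is new wording in section 2.9 and a little programming; the scheduled visits already supply the data. The replacement methods assume that loss is at random given the observed data, and the plan should say so.
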